#### Software component

The MySQL relational database management system will be used to store data in the system. The database is used to contain data regarding the patients and therapists such as log-in information. In addition, exercises selected and remotely prescribed by the therapist, and the sensor and video data on the exercises performed by the patients are also stored in the database.

### Patient interface

The user interface for the patient was designed to be simple and intuitive. A patient guide is provided within the application if the patient needs additional help on its usage. Three languages are provided: English, Chinese and Malay, to cater to the diverse ethnic groups in Singapore. Before the exercises, the iPad needs to be connected to the internet. A log-in is not required as the iPad’s unique identifier is registered to the patient before the initial set-up at the participant’s house (Fig. 2a). After starting the patient application, the application ensures that sensors are detached from the charging cables (Fig. 2b and c) and are properly worn on the patient before commencement of exercises (Fig. 2d). The patient will press the ‘Begin Exercise’ button, followed by the ‘Play button’ in the next screen to commerce the exercises (Fig. 2e). The number of repetitions as performed by the patient is captured and monitored by the sensors. Visual and audio feedback is given to the patient for every repetition that exceeds the target angle set by the therapist.

**Fig. 2 Fig2:**
[figure not shown]
Usage Flow For Patient User Interface. **a** Patient is to press the ‘Play’ button to begin after starting the application. **b** Patient is directed to this page, which prompts him or her to disconnect the limb sensors from the charging cables. After which, the patient is to press the next button in (**c**) to commence. **d** Instruction is provided on how to wear the limb sensors prior to the exercise. **e** Patient is brought to this page to begin their exercise. A demonstration video is provided on the left side of the screen. The patient can look at himself or herself doing the exercises on the right side of the screen. Visual and audio feedback is also provided to patients

Additionally, another application is created for the patients to practise and familiarize themselves with the exercises prescribed prior to the actual exercise regime. Videos of the prescribed exercises are provided in the application (Fig. 3). When the tele-therapists change the prescribed exercises for the patients, the videos in the application will automatically be uploaded onto the patient’s user interface in accordance and sequence to the latest prescription.

**Fig. 3 Fig3:**
[figure not shown]
Screenshot of Video Application for Patient. The application allows patients to be familiarized with the exercises before proceeding to the actual exercise regime

### Tele-therapist interface

The user interface for the tele-therapist was designed for efficient display of information on exercises performed by patients. The application allows the tele-therapist to initiate a Facetime video call during a scheduled tele-consultation. On selecting the patient’s name, the tele-therapist will be directed to a page to remotely prescribe exercises and adjust the difficulty (progression) level and the minimum range of motion for each exercise. A summary of the rehabilitative exercises completed by the patient will be presented in graphs for easy interpretation of adherence to prescribed exercise and quality of exercises by the tele-therapist. This is in addition to the videos of patients performing the exercises. The tele-therapist can enter also clinical notes and parameters in the application to record a tele-consultation.

### Web-based data entry

A website was devised for the usage by both the research assistants and the study coordinator. The website allows research assistants to enter baseline data, primary and secondary outcome data, and tele-therapist to document patient’s clinical information during the assessment. Only the study coordinator is allowed to view all patients’ and therapists’ information and update the information in the event of data entry error. Any amendment of data entered will be recorded and date/time-stamped. In addition, the study coordinator can designate therapists and research assistants to the patients. In the occasion when an adverse event happens, the study coordinator will enter the details in the adverse events log in the application.

#### Progressive rehabilitative exercises

The tele-rehabilitation intervention group will receive a standardized rehabilitation programme for three months, which was based on the rehabilitation programme for the control group in a randomized controlled trial on weight-supported locomotion by Duncan et al. [21]. The types of exercises are summarized in Table 2. The programme comprises of both physiotherapy (Category I to IV) and occupational therapy components (Category V). Each tele-session may cover up to all five categories of exercises. The difficulty level and minimum range of motion desired for each exercise prescribed is determined by the tele-therapist who will assess and inform the patient of the change before increasing the difficulty level.

**Table 2 Tab2:** Progressive rehabilitative exercises for intervention group

Category no.	Category description	Exercise	Levels
I	Upper Limb Strengthening	Shoulder Flexion Shoulder Extension Shoulder External Rotation Shoulder Abduction Elbow Flexion Shoulder Extension Wrist Flexion Wrist Extension Wrist Pronation Wrist Supination Fingers Mass Extension	1. Gravity eliminated, active assisted 2. Gravity eliminated, active 3. Against gravity, no Thera Tube (TT) 4. Against gravity, yellow TT 5. Against gravity, red TT 6. Against gravity, green TT 7. Against gravity, blue TT
II	Lower Limb Strengthening	Hip Flexion Hip Extension Hip Abduction Knee Flexion Knee Extension Ankle Dorsiflexion Ankle Plantarflexion	1. Gravity eliminated, active assisted 2. Gravity eliminated, active 3. Against gravity, no Thera Tube (TT) 4. Against gravity, yellow TT 5. Against gravity, red TT 6. Against gravity, green TT 7. Against gravity, blue TT
III	Seated Balance Exercise		1. Equal weight bearing on ischial tuberosities for 30 seconds 2. Weight shift, lifting alternate leg from chair for 30 seconds 3. Non-paretic Upper Limb: Ipsi-lateral diagonal reaching (anterior and posterior) 4. Paretic Upper Limb: Contra-lateral diagonal reaching (anterior and posterior) 5. Non-paretic Upper Limb: Contra-lateral anterior diagonal reaching (anterior and posterior) 6. Paretic Upper Limb: Ipsi-lateral reaching (anterior and posterior)
IV	Standing Balance Exercise		1. Shoulder- width stance 30 seconds, eyes open, for 30 seconds 2. Feet together 30 seconds, eyes open 3. Staggered stance, Paretic leg in fronton step, eyes open for 30 seconds 4. Staggered stance, Non- paretic leg in fronton step, eyes open for 30 seconds 5. Semi tandem with paretic leg in front for 30 seconds 6. Semi tandem with non-paretic leg in front for 30 seconds
V	Functional Activities	Walking (Lower Limbs)	As much as possible

### Usual care

Stroke patients in Singapore typically receive acute stroke care in an acute hospital, which usually has a dedicated stroke unit. Those who are totally dependent or fully independent in activities of daily living (ADL) usually do not receive post-stroke rehabilitation. Those who are mild to moderately dependent in ADL are usually referred for centre-based rehabilitation after discharge from acute hospital. For those who are moderately to severely dependent in ADL, they usually receive inpatient rehabilitation for 4–6 weeks at inpatient rehabilitation hospitals after discharge from the acute stroke unit. These moderately to severely ADL dependent patients usually would have recovered to become mild to moderately ADL dependent during their inpatient rehabilitation hospitals stay, and hence would be referred for centre-based rehabilitation after being discharged home from inpatient rehabilitation hospitals. In acute hospitals, rehabilitation is usually started soon after stabilization of stroke and would be provided once a day for a total of 1–2 h a day by a physiotherapist and occupational therapist. In inpatient rehabilitation hospitals, rehabilitation is continued upon admission and would be provided twice a day for a total of 2–3 h a day by a physiotherapist and occupational therapist. After discharge, it usually takes 1–2 weeks for centre-based rehabilitation to be initiated and this is usually provided 1–2 times a week for an hour each time.

Home rehabilitation in Singapore is relatively under-developed and generally unavailable and unaffordable for the majority of stroke patients. Government subsidies for acute hospital and inpatient rehabilitation hospital stays are available, and government subsidies for centre-based rehabilitation are also available. However, government subsidies for home rehabilitation, previously unavailable, were only made available mid-way through this trial in July 2014.

It should be noted that for ethical reasons, the intervention group is allowed to supplement their tele-rehabilitation sessions with centre-based rehabilitation if they desire. To control for this at the data analysis stage, we will capture data on the total number of hours of use of centre-based and home rehabilitation for both intervention and control groups throughout the six months from study recruitment.

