**Methods/design:**

This is a single blind (evaluator blinded), parallel, two-arm randomised controlled trial study design involving 100 recent stroke patients. The inclusion criteria are age ≥40 years, having caregiver support and recent stroke defined as stroke diagnosis within 4 weeks. Consenting participants will be randomized with varying block size of 4 or 6 assuming a 1:1 treatment allocation with the participating centre as the stratification factor. The baseline assessment will be done within 4 weeks of stroke onset, followed by follow-up assessments at 3 and 6 months. The tele-rehabilitation intervention lasts for 3 months and includes exercise 5-days-a-week using an iPad-based system that allows recording of daily exercise with video and sensor data and weekly video-conferencing with tele-therapists after data review. Those allocated to the control group will receive usual care. The primary outcome measure is improvement in life task’s social activity participation at three months as measured by the disability component of the Jette Late Life Functional and Disability Instrument (LLFDI). Secondary outcome variables consist of gait speed (Timed 5-Meter Walk Test) and endurance (Two-Minute Walk test), performance of basic activities of daily living (Shah-modified Barthel Index), balance confidence (Activities-Specific Balance Confidence Scale), patient self-reported health-related quality-of-life [Euro-QOL (EQ-5D)], health service utilization (Singapore Stroke Study Health Service Utilization Form) and caregiver reported stress (Zarit Caregiver Burden Inventory).

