Given the current heterogeneity and room for improvements in solutions related to post-stroke rehabilitation, there is a need for well-designed intervention and rigorous trial to close the gap. The Singapore Tele-technology Aided Rehabilitation in Stroke (STARS) Study is a parallel, two-arm (intervention-control), single blind (evaluator-blind) randomised controlled trial to determine if a novel tele-rehabilitation intervention can improve functional recovery of post-stroke patients. For the tele-rehabilitation intervention arm of this study, the team developed small affordable lightweight wireless wearable sensors which can be strapped onto patients to allow real-time biofeedback and collection of sensor data from the sensors for subsequent transmission to patient’s rehabilitation team wirelessly via the internet. The sensor data is automatically summarized in chart form for quick review by therapist to allow them to prescribe further rehabilitation exercises remotely. The system also automatically allows the patient to self-record videos of them exercising which will also be transmitted to the therapist (termed ‘tele-therapist’) for review where needed, and allow patients and their therapists to communicate with each other using video-conferencing. The study’s primary hypothesis is that this novel tele-rehabilitation intervention during the first three months after stroke admission will result in greater functional recovery compared to usual care three months after stroke admission, as determined by the Jette Late Life Functional and Disability Instrument (LLFDI). Secondary hypotheses are that tele-rehabilitation intervention during the first three months after stroke admission will result in greater functional recovery as determined by gait speed, 2-min walk test and Shah modified Barthel Index, less health service utilization, greater contact time with therapist, better balance, better quality of life, less caregiver burden and be more cost-effective compared to usual care three months after stroke admission. Process measures in the form of a diary will be used to assess improved adherence in rehabilitation. Outcomes will also be assessed again at six months post-stroke to determine whether any improvement in outcomes is sustained in both groups.

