#### Analysis for outcome measures

Data entered will be checked for accuracy at least twice by at least two independent assessors. To understand the structure of missing data and to reduce bias from uncertainty of missing data, multiple imputations will be performed using the Markov Chain Monte Carlo method. All scale-based measures used in this study will be screened via an internal consistency test (Cronbach’s alpha test) before creating a summative score. Furthermore, rigorous validity tests will be performed in two ways: person-centered tests (latent class analysis) and variable-centered tests (exploratory and confirmatory factor analyses).

For descriptive statistics, independent two-sample *t*-test and Analysis of Covariance (ANCOVA) will be performed on all continuous outcome measures (i.e. Shah-modified BI, ABC Scale, gait speed, two-minute walk test and ZBI) between tele-rehabilitation vs. usual care group if outcomes are normally distributed. Mann–Whitney *U* test will be performed on data with skewed distribution to test differences between treatment groups. Chi-square test will be performed on categorical variables. Confounders are age, gender, ethnicity and marital status. Multiple linear regressions will be used to adjust for differences in confounders between intervention and control groups for continuous outcome variables. Ordered logistic regressions will be used to adjust for differences between intervention and control groups for continuous categorical variables. For these multivariate linear and logistic regressions, we will use survey analysis processes with robust standard errors which accounts for nesting effects within patient data as a result of clustering by different recruitment centers. For all statistical analyses, the level of significance (α) will be taken at 0.05. Analyses will be based on the intention-to-treat approach. We will use STATA version 12 for statistical analysis and significance level is set at P < 0.05.

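### The protocol states an intent to control for rehabilitation hours used after randomisation and does not reconcile it with intention to treat; adjusting the treatment comparison for those hours would bias it

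*Protocol article*

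**What the plan says.** Protocol article, Usual care: for ethical reasons, "the intervention group is allowed to supplement their tele-rehabilitation sessions with centre-based rehabilitation if they desire". The next sentence reads "To control for this at the data analysis stage, we will capture data on the total number of hours of use". This refers to rehabilitation at a centre or at home, and the data are collected "for both intervention and control groups throughout the six months from study recruitment".

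Protocol article, Analysis for outcome measures: "Analyses will be based on the intention-to-treat approach". The covariates are named in the same section: "Confounders are age, gender, ethnicity and marital status". Rehabilitation hours do not appear there.

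On timing, the Abstract says "The primary outcome measure is improvement in life task’s social activity participation at three months", and the Background adds "Outcomes will also be assessed again at six months post-stroke".

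Three other places bear on the point:

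- The Background lists among the hypothesised effects of the intervention "less health service utilization, greater contact time with therapist, better balance, better quality of life".
- Process measures describes a diary of daily therapy minutes.
- The Discussion asks, as a separate aim, whether any functional gain works through better adherence to supervised exercise.

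**The concern.** Hours of centre-based and home rehabilitation are not a baseline characteristic. They accrue after randomisation and can be changed by it, because remote sessions may replace centre visits or prompt them. They also follow the patient's progress. The Usual care section itself says that fully independent and totally dependent patients usually get no post-stroke rehabilitation, while those in between are referred to a centre.

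Permitted top-up sessions are part of what offering tele-rehabilitation leads to in this trial. The intention-to-treat comparison already includes their effect, so nothing is left to remove from it. Holding hours constant takes out whatever part of the effect runs through hours. Where an unmeasured recovery factor drives both hours and outcome, it also makes the arms differ on that factor.

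What is at stake is the interpretation of the main result. An analyst following the Usual care sentence and one following the analysis section could report different treatment effects, each in line with the protocol.

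**Working it through.** The protocol gives no figure for this point, so there is none to reproduce. The check compares the passages and then uses two illustrations. All parameters are assumptions, except that the scale (SD 16) and an effect of 8 points are borrowed from the Sample size section.

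**1. Passages side by side**

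- Usual care gives the purpose (control, at the analysis stage) and the variable (hours in both arms over six months). It gives no model, outcome or time point.
- Analysis for outcome measures gives the principle (intention to treat) and the covariates (four demographic variables). It mentions hours neither to include nor to exclude them.
- The Background hypothesises less service use and more therapist contact under the intervention. By the protocol's own account, then, allocation may move these hours, and the direction for centre-based and home hours is not fixed.

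**2. Illustration A: hours up to the outcome visit**

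Let T be the arm (0 or 1), U unmeasured recovery (SD 1, independent of T) and H hours. One outcome unit is 16 points.

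- H = -0.5T + gU + e, with SD of e = 1
- Y = 0.5T + 0.1H + 0.5U + error

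Total (intention-to-treat) effect: 0.5 + 0.1 × (-0.5) = 0.45, or 7.2 points, whatever g is.

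Given T and H, the expected value of U is g(H + 0.5T)/(1 + g²). The coefficient of T adjusted for H is therefore 0.5 + 0.5 × 0.5 × g/(1 + g²) = 0.5 + 0.25g/(1 + g²).

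| g | Adjusted coefficient | Points (× 16) | Against 7.2 |
|---|---|---|---|
| 0 | 0.50 | 8.0 | +11% |
| -0.5 | 0.50 - 0.125/1.25 = 0.40 | 6.4 | -11% |
| +0.5 | 0.50 + 0.125/1.25 = 0.60 | 9.6 | +33% |

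**3. Illustration B: other assumed values, total effect fixed at 8 points**

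- H = 10 + aT + cU + 5e
- Y = (8 - 0.3a)T + 0.3H + 5U + 9.6 × baseline + 10 × error

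By the same algebra, the coefficient of T adjusted for hours to three months is 8 - 0.3a - 5ac/(c² + 25). For example, a = 5 and c = 2 give 8 - 1.5 - 50/29 = 4.8; a = -5 and c = 2 give 8 + 1.5 + 50/29 = 11.2.

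For the six-month total, hours in months 3 to 6 are set to 5, less 0.2 for each point by which the three-month outcome exceeds its mean, plus noise of SD 4. The last column comes from simulation with 400,000 patients per scenario; the unadjusted estimate stayed between 7.94 and 8.05 throughout.

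| a (arm difference in hours) | c (recovery link) | Adjusted for hours to 3 months | Adjusted for 6-month total |
|---|---|---|---|
| -5 | -2 | 7.8 | 4.7 |
| -5 | 0 | 9.5 | 5.3 |
| -5 | 2 | 11.2 | 6.8 |
| 0 | -2 | 8.0 | 7.2 |
| 0 | 0 | 8.0 | 7.3 |
| 0 | 2 | 8.0 | 7.7 |
| 5 | -2 | 8.2 | 9.8 |
| 5 | 0 | 6.5 | 9.4 |
| 5 | 2 | 4.8 | 8.7 |

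**4. What this shows**

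The error can go either way. It vanishes for hours to three months when those hours do not differ by arm. With the six-month total it remains even then, because the later hours are themselves shaped by the outcome being analysed.

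**The case against.** The best reply is that the Usual care sentence commits only to capturing data. The covariates are named elsewhere without hours, the same section commits to intention to treat, and an hours-adjusted analysis could sit beside the main one in an analysis plan that is not shown. The Discussion also gives hours a legitimate second use in its question about adherence.

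Much of this stands, and it limits the point. A reader might infer any of the following, and the document supports none of them:

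- **That hours enter the primary model.** No passage says so.
- **That the three-month outcome is adjusted for hours from months 3 to 6.** Six months is the capture window. It also serves the six-month assessment and the cost analysis over the study period, and daily diary minutes would allow a cut at three months.
- **That the protocol abandons intention to treat.** The two statements are unreconciled; neither cancels the other.
- **That an hours-adjusted estimate can never be a valid direct effect.** With g = 0 in illustration A, it returns exactly the assumed direct effect of 8.0. Validity depends on whether hours and outcome share unmeasured causes.

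What does not stand is the claim that this is merely detail left to an analysis plan. The protocol itself states the purpose of collecting the hours, and that purpose is control at the analysis stage. The reason given, that the intervention arm may add centre-based sessions, concerns the comparison between arms rather than a question about mechanism.

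**Conclusion.** The point holds in conditional form. The protocol announces an intent to control for a post-randomisation variable, promises intention to treat, and does not say how the two fit together. If the treatment comparison were adjusted for these hours, it would no longer estimate the intention-to-treat effect and could be biased up or down. If the six-month total were used for the three-month outcome, the comparison would also condition on events after that outcome.

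Neither size nor direction can be derived from the documents. The illustrated ranges are 6.4 to 9.6 against a true 7.2 and, for hours to three months, 4.8 to 11.2 against a true 8. They rest wholly on assumed arm differences in hours, an assumed value per hour and assumed links to recovery. They show that the error could matter, not how large it will be. The gap should be closed before analysis; it does not invalidate the design.

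**What to change.** In Usual care, replace the stated purpose of controlling for hours with that of describing them. In Analysis for outcome measures, add wording such as:

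> The primary and secondary treatment comparisons are not adjusted for rehabilitation hours or for any other variable measured after randomisation. Hours of centre-based and home rehabilitation are reported by arm as a process measure. Any analysis adjusted for hours is an exploratory mediation analysis, labelled as such, and uses only hours accrued before the outcome visit concerned.

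The exploratory analysis would take up the adherence question raised in the Discussion and should state its assumption about unmeasured common causes of hours and outcome. The cost is a few sentences. Data collection is unchanged, and every stated aim is kept.
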